### Sample size

Thirty patients will be recruited in each of the study groups, the main constraints being the number of available devices and the number of potential patients fulfilling the inclusion criteria in the Bilbao Primary Care Health Region. Thus, if 30 patients are included in each group, and a 10% loss to follow-up is assumed at 12 months (based on previous analysis of mortality and other causes of loss in patients with similar characteristics), we have estimated a statistical power of 72% to detect significant differences between the CG and the IG in the mean number of total admissions with a level of significance of 5%. For the power calculation, it has been assumed that the mean number of admissions in the CG is 3.5, the standard deviation 1.7, and there will be a 35% decrease of hospitalisations in the IG with respect to the CG [32-34]. The power calculations have been performed with the sample size calculation software Ene 2.0.

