#### Description of the baseline characteristics of the patients

The unit of the study is the patient. The following statistics will be used for the descriptive analysis: mean, standard deviation, median and rank for the quantitative variables, and frequency and percentage for the qualitative variables. Socio-demographic and baseline clinical data will be compared between the two groups in order to test the homogeneity. Losses occurring during the study will be analysed and the main baseline characteristics of dropouts will be compared to those who have completed the study. For the comparison of quantitative variables, the Student's t-test and the non-parametric Mann Whitney U test will be used for normally and non-normally distributed data, respectively. The Chi-square or the Fisher's exact tests will be used for the comparison of qualitative variables. The level of statistical significance will be set at p < 0.05.

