#### Analysis of the main outcome measure and impact on the use of the health care services

Firstly, at 3, 6 and 12 months follow-up, a descriptive analysis of the primary and secondary outcome measures will be carried out in the two study groups (number of hospital admissions, duration of the hospital stay and mortality rate). The variables related to the use of health care services, clinical efficacy, functional status of the patients (BI), the health related quality of life -HRQL- (EQ-5D) and the family/caregiver burden (ZBI) will also be analysed. Additionally, given that certain variables will have different follow-up periods, the incidence-rates of certain variables, such as mortality, hospital admissions, visits and episodes of worsening will be calculated.

Subsequently, both primary and secondary outcome measures will be compared between the two groups of patients at each follow-up point to test whether significant differences exist. Any changes in the functional condition (BI) or HRQL of the patients (EQ-5D) and caregiver burden (ZBI) with respect to the baseline levels will also be assessed at 3, 6 and 12 months (*i.e*., difference between the follow-up and initial scores). Quantitative variables will be compared using the Student t-test or the non-parametric Mann Whitney U test, while qualitative variables will be assessed using the Chi-Square or Fisher's exact tests. The Student's paired t-test will be used to compare the differences between the baseline scores on the BI, the EQ-5D and the ZBI and the scores obtained at 3, 6 and 12 months follow-up, for each group of patients.

If statistically significant differences are detected between the CG and the IG for the baseline characteristics analysed, the comparisons of the main outcome measures will be adjusted by the corresponding baseline variables. A logistic regression model will be used to compare dichotomous categorical variables (such as, mortality), while a general linear model will be used for quantitative variables (such as, the duration of hospital stay). In the latter case, the dependant variable will be appropriately transformed if it does not fit the normal distribution. Finally, multilevel analysis will be performed to test the effect of the individual primary care professionals involved and the clinical practice site on the results.

Whenever possible, the number needed to treat (NNT) will be calculated for the primary outcome variable (number of hospital admissions).

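### Baseline significance tests decide which covariates enter the main comparisons, so chance imbalance selects the model and known prognostic factors, including the randomisation stratum, are not fixed in advance

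*Protocol article*

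**What the plan says.** Under Description of the baseline characteristics of the patients, the protocol article states: "Socio-demographic and baseline clinical data will be compared between the two groups in order to test the homogeneity". The threshold follows in the same section: "The level of statistical significance will be set at p < 0.05".

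Under Analysis of the main outcome measure and impact on the use of the health care services, the default is an unadjusted comparison: "Quantitative variables will be compared using the Student t-test or the non-parametric Mann Whitney U test". A condition comes next. "If statistically significant differences are detected between the CG and the IG for the baseline characteristics analysed", then "the comparisons of the main outcome measures will be adjusted by the corresponding baseline variables", by logistic regression for dichotomous outcomes and a general linear model for quantitative ones.

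Two other places bear on this. The Randomisation section stratifies by disease (heart failure, chronic lung disease or both), but disease is not a fixed term in the primary comparison. Assessment of the effectiveness adjusts QALYs for baseline utility without any test, on the ground that the two are strongly correlated. The multilevel analysis of professionals and practice sites is a separate final step and does not alter the rule.

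**The concern.** A covariate earns its place in the analysis of a randomised trial by predicting the outcome. A baseline p-value measures only how unevenly chance has spread the variable. Using it as the gate has three consequences.

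- A variable unrelated to admissions is adjusted for if it happens to differ, at a cost in precision.
- A variable that predicts admissions is left out if its imbalance misses p < 0.05. With 60 patients that imbalance can still be sizeable. Even when it is small, the precision that adjustment would bring is lost.
- The form of the main analysis is not known until the baseline data are in. When the rule fires there are two results, and the article does not say which is primary.

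This matters more here because the planned power is modest and recruitment is limited by devices and eligible patients. A few points of power from variables already collected are worth having.

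**Working it through.** **Inputs from the Sample size section.** "Thirty patients will be recruited in each of the study groups" and "a 10% loss to follow-up is assumed at 12 months", so 30 × 0.9 = 27 per group are analysed. Control mean 3.5, SD 1.7, 35% reduction: difference 0.35 × 3.5 = 1.225. Significance level 5%; two-sided is assumed because the article does not say.

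**The plan's own figure.** The article says "we have estimated a statistical power of 72% to detect significant differences between the CG and the IG". The noncentrality is 1.225 / (1.7 × √(2/27)) = 2.648, and the noncentral t with 52 df gives 73.8%. With 26 per group it gives 72.2%. The stated figure is reproduced to within two points.

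**How often the rule fires.** Initial assessment and baseline data lists about 16 testable items, leaving out centre, professionals and the stratified disease: age, gender, living arrangements, caregiver, relationship to caregiver, education, adverse social factors, FEV1, NYHA class, ejection fraction, home oxygen, drugs, adherence, Barthel Index, EQ-5D and Zarit. Counting caregiver and relationship as one gives 15. If the tests are independent, the chance of at least one positive is 1 − 0.95^15 = 54% or 1 − 0.95^16 = 56%.

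**Imbalance that can stay unadjusted.** The largest non-significant difference with 27 per group is t(0.975, 52) × √(2/27) = 2.007 × 0.272 = 0.546 SD (0.517 SD if all 30 per group are tested). For a variable correlated r with admissions, the shift in the estimate is 0.546 × r × 1.7:

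- r = 0.3: 0.28 admissions (23% of 1.225)
- r = 0.4: 0.37 (30%)
- r = 0.5: 0.46 (38%)

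These are maxima. The mean non-significant imbalance is about 0.20 SD, which gives 0.20 × 1.7 × 0.3 = 0.10 to 0.20 × 1.7 × 0.5 = 0.17 admissions (8 to 14%), in either direction.

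**Power.** Simulation of 8,000 trials per row: 27 per group, normal outcome with SD 1.7, difference 1.225, 16 independent normal covariates, the first two correlated with the outcome as shown and the other 14 unrelated. The correlations are assumptions; the article gives none. The last column adds a balanced, non-prognostic three-level stratum to the two covariates, 4 df in all. Monte Carlo standard error is about 0.5 points or less.

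| Correlations | Unadjusted | Stated rule | Two fixed | Two fixed + stratum |
|---|---|---|---|---|
| 0, 0 | 74.3% | 70.4% | 72.2% | 72.0% |
| 0.1, 0.1 | 73.7% | 70.2% | 73.3% | 73.0% |
| 0.2, 0.2 | 73.9% | 70.5% | 76.0% | 75.7% |
| 0.3, 0.3 | 73.7% | 70.7% | 80.5% | 80.5% |
| 0.4, 0.3 | 73.9% | 71.3% | 83.9% | 84.0% |
| 0.5, 0.2 | 74.0% | 71.1% | 86.0% | 85.9% |

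The rule fired in 54.9% of trials and disagreed with the unadjusted test on significance in 7 to 8%. With no treatment effect it rejected in 4.3 to 5.2% of trials.

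**Where the ordering changes.** If the only variable tested is itself prognostic, the rule is marginally better than no adjustment: 74.0 v 73.8% at r = 0.3, 74.3 v 73.5% at r = 0.5, 75.2 v 73.4% at r = 0.7 (20,000 trials each). If all of 15 mostly unrelated covariates are fixed, power is 70.8 to 72.0%, about the same as the rule (71.3 to 71.4%).

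**The case against.** Several points can fairly be made for the plan.

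- **Error control is intact.** The trigger uses baseline data only, and the analysts are blinded to allocation, so the rule offers no route to choosing a model by its outcome result. Type I error stays near or slightly below 5%. This stands.
- **Chance imbalance is not bias.** Over repeated randomisations the unadjusted estimate is centred correctly. The shifts above belong to individual trials and are upper limits. This stands.
- **The firing rate is an upper figure.** Many of the listed items are related (Barthel and EQ-5D, for example), and Fisher's exact test in 60 patients rejects less often than 5%. This stands.
- **Gains from fixed covariates are not assured.** The population is narrow (home care patients with at least two admissions in the previous year), so age or function may predict little. At correlations of 0.1 there is no gain. This stands too.
- **The unadjusted comparison is specified first.** One could read the adjusted one as secondary. The text does not say so, and that ambiguity is part of the problem.

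A reader might infer that the rule always has less power than both no adjustment and any fixed model. The figures do not support that: the ordering depends on how many tested variables are unrelated to admissions and on the fixed set being short and prognostic. None of these points defends a baseline p-value as a way to choose covariates.

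**Conclusion.** The concern holds as a badly chosen rule that the article states expressly; it is not a detail left to the analysis plan. The adjustment set is chosen by chance imbalance, the stratification factor is not fixed in the primary model, and the status of the adjusted result is open. The article's own QALY analysis follows the sounder principle.

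The size is moderate. If most tested variables are unrelated to admissions, the rule costs about 2 to 4 points of power against no adjustment. Against two covariates fixed in advance it costs about 3 points at correlations of 0.1 and up to about 15 at the strongest correlations assumed. These figures rest on assumed correlations, independent covariates and a normal outcome, whereas admissions are counts. They do not support a claim of inflated type I error or systematic bias. The 80 to 86% figures are what correlations of 0.2 to 0.5 would give, not a forecast for any named covariates. The change should be made, but the trial is not invalid without it.

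**What to change.** Delete the significance trigger in the main-outcome section and the homogeneity tests in the baseline section, and present the baseline table without p-values. Name one primary model in advance, adjusted for disease stratum and one or two baseline variables that are recorded in all patients and expected to predict admissions, for example age and baseline Barthel Index, whatever imbalance is observed. The severity measures suit this less well, because they are disease-specific and collected only where available. Report the unadjusted comparison as a sensitivity analysis, and say that the adjusted one is primary.

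The cost is wording only, since the data are already to be collected. The downside is a few degrees of freedom: about 1 point of power at correlations of 0.1, and about 2 points (74.3 to 72.0%) if the chosen covariates prove wholly unrelated to admissions. The list should therefore stay short.

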#### Outcome measures

All the outcome measures will be collected after 3, 6 and 12 months of follow-up, except for satisfaction with the telemonitoring technology, which will be measured only once (approximately after 3 months from the start of the study). Table 2 shows a summary of the outcome variables that will be evaluated in the present study.

**Table 2 T2:** Summary of the outcome measures analysed in the study.

	Primary outcome measure	Secondary outcome measures
**Mortality**		- Mortality due to any cause
		- Mortality due to HF or CLD
		
**Use of health care resources**	- Hospital admissions due to any cause	**- **Hospital admissions due to HF or CLD
		- Duration of hospital stay
		- Emergency department visits
		- Home visits by GP or nurses
		- Visits to primary care centres by family or caregivers
		- Telephone contacts with professionals
		- Visits to specialist doctors
		
**Clinical efficacy**		- Worsening of the patients' pulmonary and/or heart condition (number of episodes)
		
**Functional status and quality of life**		- Patient Quality of Life (EQ-5D questionnaire)
		- Functional status (Barthel Index)
		- Caregiver burden (Zarit Burden Interview)
		
**Cost-effectiveness**		- Cost-effectiveness (using QALYs)
		
**Satisfaction with the new technology**		- Degree of satisfaction of patients and health care professionals
		
**Compliance**		- Patient and provider compliance with the telemonitoring

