Compliance with telemonitoring will be evaluated through the analysis of the frequency of data transmitted by patients and the number of times that health care professionals access the telemonitoring Web-platform. Additionally, the reliability and performance of the telemonitoring system will be assessed (malfunctions of the system, problems concerning the transfer, reception and visualisation of data). The security of the system will also be evaluated (external attacks to the transmission system or server, etc.).

The reasons for the *losses *occurred during the study will be recorded. It is envisaged that such losses may include patients moving house or dying, failure to correctly manage the system, technical problems, requirements for specific health care (for example, patients in need of palliative care at home) and institutionalisation. Additionally, data concerning eligible patients or professionals who declined to participate in the study and the reasons for not participating in the study will be recorded.

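### The adjusted logistic regression for mortality would rest on about six deaths or fewer, so its treatment odds ratio will be very unstable and sometimes not estimable.

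*Protocol article*

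**What the plan says.** The section on analysis of the main outcome measure sets out two steps. Primary and secondary outcomes are first compared between arms at 3, 6 and 12 months, with the Chi-square or Fisher's exact test for qualitative variables. If baseline characteristics differ significantly between arms, comparisons are then adjusted for the variables concerned. For that step the text reads "A logistic regression model will be used to compare dichotomous categorical variables (such as, mortality"). Every variable that differs enters, with no upper limit, and nothing is said about sparse events or how the model is estimated. The Statistical Analysis section names PASW Statistics 18 as the software.

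The Sample size section supplies the numbers. "Thirty patients will be recruited in each of the study groups", and "a 10% loss to follow-up is assumed at 12 months (based on previous analysis of mortality and other causes of loss" in similar patients). The last paragraph on secondary outcomes confirms that deaths count among the losses: "such losses may include patients moving house or dying".

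Mortality is a secondary outcome. Table 2 lists it for any cause and also separately as "Mortality due to HF or CLD".

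**The concern.** A logistic model estimates the arm effect from the deaths. If one arm has none, the maximum-likelihood odds ratio is zero or infinite. If a covariate level has none, that covariate's coefficient diverges. Short of that, six deaths shared between an arm term and one covariate leave three per term.

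The plan's own loss allowance points to this range, and the model may take on as many covariates as happen to differ. The Background reports higher mortality with telemonitoring in COPD and lower all-cause mortality in HF, so readers will look at this comparison although it is secondary. An odds ratio that is infinite or swings on a single death could end up beside, or in place of, a sound exact test.

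**Working it through.** **Inputs.** From Sample size: 30 patients per arm, 10% loss at 12 months including deaths, control mean 3.5 admissions, SD 1.7, 35% reduction, 5% significance (taken as two-sided), stated power 72%.

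**Step 1: the plan's own figure.** The difference is 0.35 × 3.5 = 1.225. With 27 per arm, 1.225 / (1.7 × √(2/27)) = 2.65.
- Normal approximation: power 75.4%.
- Noncentral t: power 73.8%.
- With the Mann-Whitney efficiency of 0.955: power 71.8%.
- With 30 per arm, noncentral t: power 78.4%.

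The stated 72% is therefore reproduced to within two points with 27 per arm. The plan does count on losing 3 per arm, 6 in all.

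**Step 2: deaths implied.** 10% of 60 is 6 if every loss is a death. Deaths due to HF or CLD are a subset. If deaths accrue evenly (an assumption), at most about 1.5 fall by month 3 and 3 by month 6.

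**Step 3: fixed number of deaths D, no true effect.** The chance that all fall in one arm is 2 × C(30,D) / C(60,D).

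| Deaths | Chance that one arm has none |
|---|---|
| 6 | 2 × 593,775 / 50,063,860 = 2.4% |
| 4 | 2 × 27,405 / 487,635 = 11.2% |
| 3 | 2 × 4,060 / 34,220 = 23.7% |
| 2 | 2 × 435 / 1,770 = 49.2% |
| 1 | 100% |

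At eight deaths it is 0.5%, and at ten 0.1%.

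**Step 4: deaths vary at random.** With the same risk p in both arms, an arm has no deaths with probability q = (1 − p)^30. Exactly one empty arm has probability 2q(1 − q), and two empty arms q².
- p = 10%: q = 0.042, so one empty arm 8.1% and both 0.2%.
- p = 5%: q = 0.215, so one empty arm 33.7% and both 4.6%.

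Simulation agrees, with the arm odds ratio lost in about 7–8% and about 33% of trials. Firth's method gave a finite estimate every time. With 10% risk in control and 5% in the intervention arm, at least one arm is empty in 24.8%.

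**Step 5: adding a covariate.** With six deaths, none falls among 18 carriers (30%) with probability C(42,6) / C(60,6) = 10.5%, and none among 12 carriers (20%) with probability C(48,6) / C(60,6) = 24.5%. Some coefficient then diverges in about 13% and 26% of trials. It is mostly the covariate's. The arm coefficient diverges in only about 2–3%.

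**Step 6: precision when the estimate exists.**
- 3 v 3 deaths: odds ratio 1.0, SE of the log √(2/3 + 2/27) = 0.86, 95% limits about 0.19 and 5.4.
- 2 v 4 deaths: odds ratio (2 × 26) / (4 × 28) = 0.46, limits about 0.08 and 2.8.

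**Step 7: how often the model runs.** Assuming 10 to 20 independent baseline tests at 5%, at least one is significant in 1 − 0.95^10 = 40% to 1 − 0.95^20 = 64% of trials, and at least two in 9–26%.

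**The case against.** A reader might infer that the model will often separate and that the mortality comparison is lost. The documents do not support this, for four reasons.
- At exactly six deaths the arm odds ratio is infinite about once in 40 trials. The 13% and 26% in step 5 mostly count a diverging covariate coefficient, which usually leaves the arm odds ratio finite.
- Six is a planning allowance from the power calculation for admissions. It is not a forecast of mortality or a cap. With eight to ten deaths the arm problem almost vanishes.
- The unadjusted comparison comes first and may use Fisher's exact test, which separation does not affect. The article also provides for incidence rates of mortality.
- The model is conditional on a baseline imbalance, concerns a secondary outcome, and would usually carry no covariate or one.

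The article also does not name the estimation method. A fallback for sparse events could stand in an analysis plan that is not shown, so its absence is not in itself a fault.

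A second tempting inference is that the p-values would be falsely significant. In simulation the Wald tests were conservative, so that reading fails too.

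These points reduce the size of the concern but do not remove it. The article does fix logistic regression with an uncapped covariate list and names mortality as its example. That choice fits poorly with the deaths its own allowance implies. Wide intervals come from having 60 patients, which the article acknowledges, and no method would cure them.

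**Conclusion.** The point holds in a limited form. On the plan's own allowance, the adjusted mortality odds ratio will be very imprecise and sometimes not estimable. With standard maximum-likelihood fitting, it is infinite in about 2% of trials at exactly six deaths, about 7–8% if deaths vary around a 10% risk, and about a third at a 5% risk. The weakness is greatest for death due to HF or CLD and for the 3- and 6-month comparisons.

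The 5% risk and the even accrual of deaths are assumptions, since the article does not split losses into deaths and other causes. The percentages apply when the adjusted model is actually fitted. What is gained by changing it is an estimate that always exists, not a narrower interval. The matter is minor and leaves the primary outcome untouched.

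**What to change.** Keep Fisher's exact test as the reported mortality comparison, for all-cause and cause-specific death, at 3, 6 and 12 months. Add the risk difference with an exact 95% confidence interval.

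If a baseline imbalance triggers an adjusted analysis of mortality, fit it by Firth penalised likelihood with arm and at most one covariate named in advance, and label it supportive.

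The cost is a change of wording in the analysis plan and a check that the chosen software can fit the penalised model. The price is that mortality will not be adjusted for several covariates, which about six deaths could not support. Intervals will remain wide.

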#### Economic analysis of the telemonitoring intervention

A cost-effectiveness analysis will be undertaken from the perspective of the health care provider. The time horizon will be of one year.

